### STUDY DESIGN

**Design:** DRES-POCAI is a patient-level, multi-clinic, randomized controlled, open-label, parallel superiority trial.

**Study Aims and hypothesis:** **Aim 1** of the study is to refine and operationalize a multi-component AI diabetic retinopathy screening intervention (DRES-POCAI) and implementation plan with physicians, clinical staff, and patients from Federally Qualified Health Clinics in South and Central San Diego. **Aim 2** to evaluate the impact of DRES-POCAI implementation in a primary care setting among underserved patients with diabetes mellitus on diabetic retinopathy screening completion. We hypothesize (Hypothesis 2.1) that randomization to DRES-POCAI intervention will result in an increase in diabetic retinopathy screening completion and diabetic retinopathy detection when compared to usual care; (Hypothesis 2.2) that participants receiving DRES-POCAI intervention will be more likely to (a) complete referrals to the eye specialist, (b) establish early stages of diabetic retinopathy, and (c) be less likely to present diabetic retinopathy complications due to early treatment; and (Hypothesis 2.3) that participants receiving DRES-POCAI intervention will demonstrate greater (a) knowledge, (b) attitudes, (c) self-efficacy and (d) patient satisfaction regarding diabetic retinopathy, autonomous diabetic retinopathy screening, and other diabetes mellitus-related services and resources.

**Setting:** Selected clinics from the Federally Qualified Health Center of San Ysidro Health in San Diego County, California.

**Randomization:** Participants will be randomized using a simple block randomization design to ensure equal (1:1) allocation between intervention and standard of care arms by clinic site. Randomization will be performed using a statistical program or randomizer app (<https://apps.apple.com/us/app/choice-maker-random-picker/id1387970091>).

**Blinding:** Study staff and study data analysts will be unblinded due to the intervention activities.

**Study population:** Study participants will be active SYH patients receiving medical care in one of DRES-POCAI's research clinic sites and meet the following inclusion/exclusion criteria.

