**Exploratory outcomes**

- Patient education/knowledge outcomes as measured at baseline and 6 months
- Comparison of EyeArt diagnostic results to DR diagnosis by an eye specialist when evaluated by both methods for each individual eye.

**Covariates:** clinic site, age, sex, prior screening history, clinical risk factors, social determinates of health, barriers to care, and diabetes knowledge and self-efficacy.

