The primary analysis will compare diabetic retinopathy screening completion between the intervention group and the standard of care group. Logistic regression will be used to estimate intervention efficacy using treatment arm as the main exposure variable and the odds ratio (OR) including 95 % CI will be presented. Hosmer and Lemeshow's approach to purposeful selection of variables will be used for final model selection.

Secondary analysis will compare diabetic retinopathy screening results between treatment arms using the same logistic regression approach as the primary analysis. Missing treatment results will be classified in this analysis and no diagnosis.

**Exploratory analysis:** Exploratory analyses will be performed to assess relationships between screening completion, screening outcomes, social determinates of health, and clinical risk factors. Changes in patient education/knowledge outcomes will be assessed using difference in

differences analysis. These analyses will be used to identify items that are most strongly related to barriers and/or compliance, and be used to refine and guide future implementation strategies.

Additionally, where both EyeArt and ICD-10 codes are available, results will be compared and shared with EyeArt, however these results will not be generalizable as only results from participants in the intervention group who received ungradable or abnormal EyeArt results and who were examined by an eye specialist and had results returned to the SYH will be available for comparison.

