| Evaluate the implementation and effectiveness of a multicomponent AI clinical intervention on diabetes and DR knowledge, attitudes, self-efficacy, and patient satisfaction.                                  | 
 
1. A 15 min-survey will be conducted at the baseline and 6 months. The survey will assess patients' knowledge, attitudes about DR (e.g., “Do you think your DM can make you blind”), self-efficacy and (“I am confident that I can: take care of my eyes”). Participants will be asked about their comfort and trust in the use and results of the novel POC-AI screening that does not involve
 
                                                                                                                                            | 
We hypothesize that our intervention strategies will exert their impact on implementation and clinical outcomes through diabetes and DR knowledge, attitudes, self-efficacy, and patient satisfaction (H2.3).
                                                                                                                                                                                                                                                                                                                                                                                                                                                                                                  |

| OBJECTIVES           | ENDPOINTS                                                                                                                                                                                                                                                                                                                                                                                                                                                                                                               | JUSTIFICATION FOR ENDPOINTS                                                                                                                                                                                                                                                                                                                                                        |

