### 4.1 OVERALL DESIGN

To evaluate the implementation and effectiveness of a multicomponent AI clinical intervention using a patient-level randomized controlled trial (RCT) for underserved patients with DM receiving medical care in FQHC clinics in South and Central San Diego.

- Compared to controls, at both follow-up points, participants receiving DRES-POCAI will report: **Hypothesis 2.1** greater screening rates of DR; expect a 10% improvement in DR adherence rates; **Hypothesis 2.2** will be more likely to (a) complete referrals to the eye specialist, (b) establish early stages of DR, and (c) less likely to present DR complications due to early treatment; and **Hypothesis 2.3** greater (a) knowledge, (b) attitudes, (c) self-efficacy and (d) patient satisfaction about DR, autonomous DR screening, and other DM-related services and resources.
- *Phase of the trial, if applicable*
  - Not applicable
- *A description of the type/design of trial to be conducted (e.g., randomized, placebo-controlled, double-blinded, parallel design, open-label, dose escalation, dose-ranging, adaptive, cluster randomized, group sequential, multi-regional, superiority or non-inferiority design)*
  - This is a randomized controlled trial (RCT). Patients will be randomized into either the intervention or usual care arm when they arrive for their appointment. A simple block randomization design will ensure equal allocations between intervention and usual care arms by clinic and assign participants to equal (1:1) allocation between arms.

Randomization will be performed using a statistical program (random number generator) to allocate study assignments.

- *A description of methods to be used to minimize bias*
  - Drs. [name] and [name] will work closely to manage any potential missing data issues, to measure and correct potential biases, including administrative and fiscal oversight.
- *Dose escalation or dose-ranging details should be contained in **Section 6.1.2, Dosing and Administration***
  - Not applicable
- *The number of study groups/arms and study intervention duration*
  - There will be two study arms as participants will be randomized to the intervention (autonomous DR screening or Standard-of-Care). The intervention is for a period of 1 year.
- *Indicate if single site or multi-site*
  - Single site working with SYHealth. Locations are the King-Chavez and Chula Vista clinics.
- *Name of study intervention(s)*

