## 4.2 SCIENTIFIC RATIONALE FOR STUDY DESIGN

The DRES-POCAI study is using a randomized controlled, open-label, parallel superiority trial. The benefit of this trial is that each participant will be randomized to two intervention options, allowing researchers to compare the relative effectiveness of multiple intervention options. The DRES-POCAI study employs a randomized controlled, open-label, parallel superiority trial design. This design is well-suited to achieve the study's aims for several reasons:

**Randomization:** Random assignment of participants to intervention and control groups minimizes confounding variables. This ensures that any observed differences in outcomes are likely due to the intervention itself and not pre-existing differences between the groups. Participants of the DRES-POCAI study will be randomized into two groups: usual care (receive a retinal screening by an optometrist) or intervention group (receive a retinal screening using a special camera and EyeArt® system, *an autonomous AI-based DR screening*). The randomization will occur after consenting and completing the surveys, prior to conducting the DR screening process (for those randomized to the intervention group).

**Open-label Design:** The open-label nature is appropriate given the practical realities of implementing a multi-component intervention with integrated technology. Blinding participants and providers to the autonomous DR screening is logistically difficult. The intervention's immediate results and potential impact on the workflow necessitate an open-label approach.

**Parallel Design:** The parallel design allows for a clear, side-by-side comparison of outcomes between the intervention and usual care groups over time. This establishes the efficacy of the multicomponent approach. Also, this approach streamlines research analysis and clearly compares outcomes within the defined study period.

**Superiority Evaluation:** The primary objective is to determine if the multi-component DRES-POCAI intervention is superior to usual care in increasing DR screenings, early detection, referrals, and patient knowledge/self-efficacy. A superiority trial directly establishes whether the intervention offers significant benefits over the current model.

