**Analysis:** We will explore the association between various demographic and clinical characteristics and knowledge, attitudes, self-efficacy, and patient satisfaction. Given the exploratory nature of this endpoint, analysis will be used to refine intervention implementation methods, identify barriers to participation, and increase participant satisfaction.

---

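### H2.3 predicts greater knowledge, attitudes and self-efficacy than in controls, but the analysis written for it does not compare the arms, and the SAP names an arm comparison only for education/knowledge

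*Combined protocol and SAP*

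**What the plan says.** Both documents state H2.3 as a contrast with usual care. Protocol Section 4.1 introduces the hypotheses with "Compared to controls, at both follow-up points, participants receiving DRES-POCAI will report", and H2.3 then predicts "greater (a) knowledge, (b) attitudes, (c) self-efficacy and (d) patient satisfaction about DR". The Study Aims paragraph of the SAP agrees: "that participants receiving DRES-POCAI intervention will demonstrate greater (a) knowledge, (b) attitudes, (c) self-efficacy and (d) patient satisfaction regarding diabetic retinopathy". The secondary objective in protocol Section 3 is to evaluate the "effectiveness of a multicomponent AI clinical intervention on diabetes and DR knowledge, attitudes, self-efficacy, and patient satisfaction". Section 4.2 says that the trial is to establish whether the intervention is "superior to usual care in increasing DR screenings, early detection, referrals, and patient knowledge/self-efficacy".

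The analyses read differently. Under the H2.3 label in protocol Section 9.4.3: "We will explore the association between various demographic and clinical characteristics and knowledge, attitudes, self-efficacy, and patient satisfaction". Sections 8.1, 9.1 and 9.4.9 relate each questionnaire item to whether screening was completed. In the SAP, the relevant entry under Exploratory outcomes is "Patient education/knowledge outcomes as measured at baseline and 6 months", and the Exploratory analysis paragraph says "Changes in patient education/knowledge outcomes will be assessed using difference in" differences.

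**The concern.** An association of age or HbA1c with a knowledge score does not show whether the intervention raised that score. Nor does an association between a questionnaire item and screening completion. An analyst who follows the H2.3 paragraph as written will have an answer to a different question.

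Two consequences follow. If attitudes or self-efficacy are later reported as different between arms, no analysis specified in advance for those outcomes stands behind the result. If they are not reported by arm, a hypothesis stated in both documents goes unanswered, although the data to address it will have been collected.

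**Working it through.** This is mainly a comparison of texts. The documents give no sample size or power for H2.3.

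**Step 1. Is H2.3 a between-arm claim?** Yes: protocol Section 4.1 and the SAP's Study Aims paragraph both say so, for four components.

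**Step 2. Set each component against the analysis specific to it.**

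| H2.3 component | Surveyed in both arms at baseline and 6 months? | Arm comparison in the protocol's H2.3 text (8.1, 9.1, 9.4.3, 9.4.9)? | Arm comparison named in the SAP? |
|---|---|---|---|
| (a) Knowledge | Yes (Sections 3, 6.1.1, 8.1) | No | Yes, difference in differences |
| (b) Attitudes | Yes (Section 3; 8.1 speaks of beliefs) | No | No, on a plain reading |
| (c) Self-efficacy | Yes (Sections 3, 8.1) | No | No; otherwise listed only as a covariate |
| (d) Satisfaction | No; the survey is for the intervention group only (4.4, 8.1) | No | No |

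Within Section 9.4 the contrast is plain. The analysis paragraphs for screening completion (9.4.2) and DR diagnosis (9.4.3) both name the two groups to be compared. The H2.3 paragraph does not.

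**Step 3. Which time point can be used?** Six months. Section 3 places the survey at baseline and 6 months, and Section 4.4 expects usual-care participants to finish within about six months.

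**Step 4. Would the missing comparison be informative?** The plan's only sample-size figure is for screening completion, and it reproduces. With 59% versus 69%, two-sided α = 0.05 and 80% power, n per arm = [1.960·√(2·0.64·0.36) + 0.842·√(0.59·0.41 + 0.69·0.31)]² / 0.10² ≈ 360.5, so 361 per arm and 722 in all.

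The same 361 per arm gives these smallest detectable differences in a numeric survey score, in SD units:

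- 6-month score alone: (1.960 + 0.842)·√(2/361) = 0.21.
- Baseline-adjusted: multiply by √(1 − r²).
- Difference in differences: multiply by √(2(1 − r)).

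Here r is the correlation between baseline and 6 months. The documents give no value, so a range is shown:

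| Assumed r | Baseline-adjusted | Difference in differences |
|---|---|---|
| 0 | 0.21 | 0.29 |
| 0.3 | 0.20 | 0.25 |
| 0.5 | 0.18 | 0.21 |
| 0.7 | 0.15 | 0.16 |

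If fewer participants return the 6-month survey, the figure for the follow-up score alone rises to 0.23 with 289 per arm (80% of 361) and 0.25 with 253 per arm (70%). Return rates are likewise an assumption. The arm comparison is therefore feasible with the planned enrolment, and adjusting for baseline is at least as precise as the difference in differences throughout this range.

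**The case against.** The strongest reply is that the protocol does compare arms in general terms. Section 9.4.1 compares an unnamed outcome of interest between groups, with arm as the main independent variable. Section 8.1 compares arms on the primary and secondary outcomes, with t tests for continuous variables, and Section 3 files the survey under secondary. Since completion is binary and DR diagnosis is categorical, t tests would suit survey scores better than either.

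This stands in part: it would be wrong to infer that the protocol nowhere compares arms. But Sections 8.1 and 9.1 name DR diagnosis as the secondary outcome and then give the survey its own analysis without arms. Section 9.4.1 offers logistic or Poisson regression and names no survey outcome. Where specific and general text differ, an analyst will follow the specific text.

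Second, education/knowledge in the SAP might mean the whole instrument. The protocol calls it the education questionnaire, and Section 8.1 groups beliefs with knowledge. The survey itself is not among the documents reviewed, so this reading cannot be excluded. Against it, the SAP's own statement of H2.3 lists knowledge, attitudes and self-efficacy separately, and its covariate list names knowledge and self-efficacy as two things.

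Third, a reader might infer that the two documents conflict on knowledge, or that the survey data go unused between arms. Neither follows. The protocol's associations and the SAP's difference in differences can both be run, and the SAP does use the knowledge data to compare arms.

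Finally, Sections 9.1 and 9.4.3 and the SAP treat these outcomes as exploratory. That lowers the stakes but does not supply the comparison.

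**Conclusion.** The point holds in a limited form. The text written to analyse H2.3 cannot answer H2.3. On the plain reading of the SAP, knowledge has a named between-arm analysis, while attitudes and self-efficacy have none in either document, although both arms are surveyed on them at baseline and 6 months. Satisfaction cannot be compared between arms as the survey is designed.

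The count of one domain in three rests on reading education/knowledge as knowledge. On the broader reading the SAP would cover all three, and what remains is an H2.3 paragraph in the protocol that omits the arm comparison and a SAP term that needs defining. The primary analysis, its α and its sample size are unaffected. This should be corrected, but it does not threaten the trial's main conclusion.

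**What to change.** - **Protocol 9.4.3, H2.3 analysis.** State that knowledge, attitudes and self-efficacy at 6 months will each be compared between randomized arms, reporting the arm effect with a 95% CI and adjusting for the baseline value and clinic. Say which items or score represent each domain. Because 9.4.3 allows nominal, binary or categorical outcomes, choose the model to suit the scale: linear for scores, logistic or ordinal for binary or categorical items.
- **SAP.** Name all three domains under Exploratory outcomes and apply the same analysis. Extending the existing difference in differences to all three is acceptable, though baseline adjustment is usually more precise.
- **Association analyses.** Keep the analyses of patient characteristics and of questionnaire items, but as a separate descriptive analysis not presented as a test of H2.3.
- **Satisfaction.** Restate H2.3(d) as descriptive in both documents, since its survey has no usual-care respondents.

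The cost is wording in the two documents and a few extra models. No new data and no change in conduct are needed, and the outcomes can stay exploratory.

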#### 9.4.4 SAFETY ANALYSES

No safety endpoints will be analyzed, however documented all adverse events will be presented as a table in the final report and will include date of adverse event, description of event, and any resolution/ follow-up/or final outcome of the event.

---

#### 9.4.5 BASELINE DESCRIPTIVE STATISTICS

At the time of enrollment, patient-level data will be collected from the participants' EHR, such as patient demographics, clinical data, and date of previous screening. Additional patient-level data will be collected in self-administered questionnaires. Baseline characteristics will be compared between intervention and usual care groups using two-sample t tests for continuous variables and Pearson's chi-squared test will be used for binary and categorical variables.

If any significant imbalance is detected for any baseline characteristics, a sensitivity analysis will be performed, and the unbalanced characteristics will be incorporated into regression outcome models.

---

#### 9.4.6 PLANNED INTERIM ANALYSES

**Not applicable.**

---

#### 9.4.7 SUB-GROUP ANALYSES

Sex and race/ethnicity will be included in both the primary (DR screening completion) and secondary (DR diagnosis) initial regression models.

---

#### 9.4.8 TABULATION OF INDIVIDUAL PARTICIPANT DATA

All data will be captured at the individual participant level and will be listed by measure. Repeated measurements will be listed by measure and time from enrollment.

---

#### 9.4.9 EXPLORATORY ANALYSES

For the survey exploratory analyses will be performed to assess relationships between each item in the **(H2.3)** education questionnaire and the screening behavior (i.e., the proportion of patients with completed DR screening). Multiple deletion or imputation methods will be used to handle missing data and will be dependent on the pattern of missingness, e.g. if entire surveys are missing if missingness is driven by specific items or response groups in the survey, and/or if the data is missing completely at random. We have allowed for a 10% dropout/withdrawal rate between enrollment and intervention, and thus can use pairwise or listwise deletion of up to 10% of participants and still maintain adequate power for analysis. These analyses will be used to identify items most strongly related to barriers and/or compliance, and thus, help refine the approach and guide future implementation strategies.

## 10 SUPPORTING DOCUMENTATION AND OPERATIONAL CONSIDERATIONS

*Leave blank. Text should be included under the relevant subheadings below.*

### 10.1 REGULATORY, ETHICAL, AND STUDY OVERSIGHT CONSIDERATIONS

*11 Leave blank. Text should be included under the relevant subheadings below.*

#### 10.1.1 STUDY DISCONTINUATION AND CLOSURE

The DRES-POCAI study may be temporarily suspended or prematurely terminated if there is sufficient reason to do so. Circumstances that could warrant suspension or termination include unexpected safety concerns for participants, demonstration of overwhelming efficacy that necessitates providing the superior intervention to all, evidence that the study intervention is unlikely to demonstrate the intended effect, insufficient compliance with study protocols, data quality issues, or decisions by the sponsor, funding agency, or regulatory bodies.

This study may be temporarily suspended or prematurely terminated if there is sufficient reasonable cause. If the study is prematurely terminated or suspended, the Principal Investigator (PI) will promptly inform study participants, the Institutional Review Board (IRB), and sponsor and will provide the reason(s) for the termination or suspension. Study participants will be contacted, as applicable, and be informed of changes to the study visit schedule.

A suspended study may resume once any concerns about safety, protocol compliance, and data quality are addressed to the satisfaction of the sponsor, IRB, and relevant regulatory agencies.

